11.2 Randomization and Blinding

Experimental group (dry group): tracheal intubation without pretreatment (n = 150)

Control group (saline group): tracheal intubation with water lubricated tube (n = 150)

After the recruitment, participants are randomly assigned to one of the two groups in a 1:1 ratio depending on whether or not the tracheal tube is lubricated with water before intubation.

A random sequence with 4 or 6 sizes of random blocks (i.e., 4-4-4-6-4-4-6-6…) is generated

with an online tool by an assistant not involved in the trial and kept within sealed opaque envelopes. When a patient is enrolled in the trial, an anesthesia nurse opens an envelope and prepares a tracheal tube with the allocated treatment.

11.3 Administration and dose of drug: N/A

11.4 Outcome measurements

- Demographic data: sex, age, body weight, height, body mass index

- airway related parameters: modified Mallampati class, Cormack-Lehane grade, thyromental distance

- ease of mask ventilation (easy/moderate/difficult)

- intubation time, duration, resistance of tube advancement

- hemodynamic parameter change before and after the intubation : mean blood pressure, heart rate, saturation

- Extubation time

- oral bleeding, blood tinged tracheal tube cuff, mechanical injury of tracheal tube

- Sore throat and hoarseness at 0, 2, 4 and 24 after the surgery

- Oropharyngeal injuries at 2 and 24 h after the surgery

- Amount of postoperative analgesics

- Symptoms of respiratory infections of diagnosis of any other respiratory infectious diseases up to 7 days after the surgery

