**11. Study protocols**

11.1 Interventions

After overnight fasting, participants enter the operating room without any premedication and standard monitoring (electrocardiography, noninvasive arterial blood pressure, and pulse oximetry) are applied. According to random allocation, a disposable tracheal tube (Unomedical, Kedah, Malaysia), which is made of polyvinyl chloride and has a cuff with high-volume and low-pressure characteristics, is pretreated by an anesthesia nurse unaware of the study protocol. Until

tracheal intubation, the tube is placed in a 1-L bottle of sterile saline for the experimental group or kept inside the sterile packing for the control group. Tubes with 7.0-mm and 7.5-mm internal diameters are used for women and men, respectively

General anesthesia is induced with intravenous administration of propofol 1.5–2.0 mg/kg and fentanyl 1 mcg/kg. Rocuronium 0.6–0.8 mg/kg is administered for the neuromuscular blockade and train of-four counts are checked at the adductor pollicis muscle using acceleromyography (TOF-watch®, Organon Ltd., Dublin, Ireland). At a train-of-four count of 0, the tracheal tube, pretreated according to the randomization, is handed to an investigator who has a 10-year experience in tracheal intubation. The investigator performs tracheal intubation via direct laryngoscopy using either Macintosh 3 or 4 blades and evaluates the Cormack-lehane grade.

I: no difficulty

II: only posterior extremity of the glottis visible

III: only the epiglottis visible

IV: no recognizable structures visible without laryngeal manipulation

The intubation practitioner subjectively evaluates the resistance during advancement of the tube through the glottis using a four-point scale (none, mild, moderate, and severe). Intubation time, defined as the duration between the insertion of the laryngoscopic blade into the mouth and the inflation of the endotracheal tube cuff, is measured. If intubation fails, the tube tip is flexed to make a hockey-stick shape by inserting the stylet inside the tube, and then intubation is reattempted. When intubation fails in 3 attempts even using the stylet, other devices such, as a video laryngoscope, fiberoptic bronchoscope, or lighted stylet, are applied. Intracuff pressure is maintained at 25 cmH_2_O. Anesthesia is maintained with 1.0–1.5 minimum alveolar

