11.6 Expected Adverse Events and Precautions for Use

In general, there is a risk of complications such as hypoxia due to delayed intubation, mucosal injury and microhemorrhage, tracheal tube cuff injury, vocal cord injury, dental damage, laryngeal pain, hoarseness, and respiratory infections. Both the water-lubricated and the dry tube method were widely used in clinical practice, and there was no difference in postoperative complications between the two methods in a previous small-case study. Therefore, it is unlikely that additional risk will arise from this study. In addition, all procedures are monitored by a trained anesthesiologist, and even if complications occur, appropriate treatment will be taken so that the possibility of additional risk to the patient is expected to be minimal.

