**12. Statistical analysis**

Both intention-to-treat and per-protocol analyses will be performed and missing data will be imputed with the last observation carried forward value. Continuous variables

will be presented as mean and standard deviation or median and interquartile range according to the Kolmogorov-Smirnov test, and categorical variables as number of patients and proportion.

The incidence of postoperative sore throat (primary outcome)

will be compared with a noninferiority analysis.The noninferiority of the nonpretreated tube over the water-lubricated tube will be accepted if the upper bound of a 95% confidence interval is below the predetermined noninferiority margin of 15%. For secondary outcomes, continuous variables will be compared with an independent t test or the Mann-Whitney U test and categorical variables with Pearson’s chi-squared test or Fisher’s exact test.

All tests are two-sided and P < 0.05 is considered statistically significant. A statistician not involved in data collection will conduct all statistical analyses using SPSS software (version 21.0, SPSS Inc., IBM, Chicago, IL, USA).

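### Saturation is listed only as a change before and after intubation, so the comparison between groups may miss a transient dip during an attempt; recording the lowest value would fit the named hypoxia risk better.

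*Protocol*

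**What the plan says.** Protocol section 11.6 opens its list of expected adverse events by saying that, in general, "there is a risk of complications such as hypoxia due to delayed intubation". Section 11.4 holds the only outcome that concerns oxygenation: "hemodynamic parameter change before and after the intubation : mean blood pressure, heart rate, saturation". That line gives no times for the readings and no lowest value, threshold or desaturation event.

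Four other statements bear on the point.

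- Section 11.1: on entry to the operating room, before induction, "standard monitoring (electrocardiography, noninvasive arterial blood pressure, and pulse oximetry) are applied".
- Section 11.1: the person intubating "subjectively evaluates the resistance during advancement of the tube through the glottis using a four-point scale". Intubation time is defined as "the duration between the insertion of the laryngoscopic blade into the mouth and the inflation of the endotracheal tube cuff, is measured".
- Sections 11.6 and 11.8: "all procedures are monitored by a trained anesthesiologist", and research-related adverse events go to the ethics board. Hypoxic brain or organ damage is given as an example of a serious event.
- Section 12: for secondary outcomes, "continuous variables will be compared with an independent t test or the Mann-Whitney U test".

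**The concern.** A before/after pair suits blood pressure and heart rate, where the question is the response to intubation. Saturation shares that line, but hypoxia from a slow or repeated attempt arises between the two readings and can resolve once ventilation starts. Section 11.1 allows reattempts with a stylet, and other devices only after three failures, so the interval between readings may be long in the patients who matter most.

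There are two separate weaknesses. The second reading may come too late to show the dip. And even a captured dip is a large change in a few patients, which a rank-based comparison of all patients may barely notice.

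The stake is limited but real. A finding of no difference in saturation change could be read as reassurance about a named risk that the measure does not target. A later analysis plan could not recover a lowest value that was never collected.

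**Working it through.** **Plan's own figure.** The protocol gives no rate, threshold or power for saturation, so there is nothing to reproduce. The only input taken from it is 150 patients per group (section 11.2).

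**Assumptions, none from the protocol.** A dip is 14 points. The before/after change is otherwise normal with mean 0 and SD 1 point. The dip rates are 3% with a lubricated tube and 10% or 8% with a dry tube; a rarer case of 1% and 3% is added. The share of dips still present at the second reading is 0, one quarter or all. Tests are two-sided at 5%.

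**Count of patients with a dip.** Power ≈ Φ(d/SE − 1.96), with SE = √{[p₁(1−p₁) + p₂(1−p₂)]/150}.

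- 3% v 10%: SE = √[(0.0291 + 0.0900)/150] = 0.0282; 0.07/0.0282 − 1.96 = 0.52; power about 70%.
- 3% v 8%: SE = √[(0.0291 + 0.0736)/150] = 0.0262; 0.05/0.0262 − 1.96 = −0.05; power about 48%.
- 1% v 3%: SE = √[(0.0099 + 0.0291)/150] = 0.0161; 0.02/0.0161 − 1.96 = −0.72; power about 24%.

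These are somewhat generous. Fisher's exact test gives about 62% and 38% in the first two cases.

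**Comparison of the change.** Share of 8,000 simulated trials that reject:

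| Dip rates | Dips caught | t test | Mann-Whitney | Count of dips |
|---|---|---|---|---|
| 3% v 10% | none | 5% | 5% | 70% |
| 3% v 10% | one in four | 16% | 6% | 70% |
| 3% v 10% | all | 68% | 18% | 70% |
| 3% v 8% | none | 5% | 5% | 48% |
| 3% v 8% | one in four | 11% | 5% | 48% |
| 3% v 8% | all | 44% | 12% | 48% |
| 1% v 3% | all | 19% | 6% | 24% |

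The count column assumes that the lowest value is recorded, so it does not depend on when a second reading is taken. The 5% in the rows with no dip caught is just the type I error.

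**Sensitivity of the Mann-Whitney figure.** It depends on the ordinary scatter of readings. With changes rounded to whole points, all dips caught and 3% v 10%, it rejects in about 19% of 4,000 trials at SD 1, 23% at SD 0.5 and 64% at SD 0.2, where nearly all other patients show exactly zero change.

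**Which test applies.** Section 12 allows either. It ties the Kolmogorov-Smirnov test to how variables are presented and does not state a rule for choosing the test. Saturation has a ceiling and skewed changes, so Mann-Whitney is the likelier choice.

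**The case against.** The strongest reply is that the loss is largely built into the assumptions. Section 11.4 does not say that there is one reading on each side, or when it is taken. A reading at cuff inflation might catch a dip, and with every dip caught the t test loses almost nothing against the count (68% v 70%). This stands: the size of the problem cannot be fixed from the protocol. It does not rescue the measure, because the times are left open and the rank test is weak under ordinary scatter even with full capture.

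The pathway is also partly covered. Resistance and intubation time are measured in every patient, an anesthesiologist monitors each procedure, and adverse events are reported. So a reader might infer that a dip would be invisible or unrecorded, but the documents do not support that: oximetry is in use, the data form is not shown, and a dip noticed clinically could be reported. The cover is indirect, though. Time and resistance measure delay and difficulty rather than desaturation, and section 11.8 sets no saturation threshold and names only severe harm.

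A reader might also take hypoxia to be the trial's main acute safety question. Section 11.6 gives a generic list of intubation risks, does not attribute hypoxia to the dry tube, and calls additional risk unlikely. The hypothesis in section 8.2 concerns sore throat.

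Finally, dips may be rare. Section 10.2 excludes expected difficult airways and section 11.1 uses an experienced operator. At 1% v 3% the count has only about 24% power. This stands too, and limits what the remedy can show.

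**Conclusion.** The point holds in a limited form. The listed saturation outcome does not target a dip between readings, so the comparison between groups may miss transient desaturation. Under Mann-Whitney, even captured rare dips may hardly register.

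For 3% v 10%, the chance of detecting the difference runs from 5% to 68% with a t test, depending on the timing of the readings, and is about 18% with Mann-Whitney and full capture at an SD of 1 point. The count gives about 70%. These figures rest on assumed dip rates, dip depth and scatter, and show the mechanism rather than what this trial would find.

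No passage contradicts another. This is a minor improvement to a secondary safety measure, with no bearing on the primary outcome, the sample size or the noninferiority conclusion.

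**What to change.** In section 11.4, keep mean blood pressure and heart rate as before/after changes and take saturation out of that line. Record instead the lowest saturation from first blade insertion to a fixed time after cuff inflation. The investigators should fix that time and a reporting threshold before the first patient. Report by arm the number of patients below the threshold, with a 95% confidence interval for the difference.

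The cost is one extra form field, read from a monitor already in use, with no change in patient care. If events are rare the interval will be wide: at 1% v 3% it is about 2 ± 3.2 percentage points (1.96 × 0.0161). The result should therefore be presented as descriptive, not as proof that the two methods are equally safe.

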11.5 Primary outcome measurements

- Incidence of sore throat during postoperative 24 h

11.6 Expected Adverse Events and Precautions for Use

In general, there is a risk of complications such as hypoxia due to delayed intubation, mucosal injury and microhemorrhage, tracheal tube cuff injury, vocal cord injury, dental damage, laryngeal pain, hoarseness, and respiratory infections. Both the water-lubricated and the dry tube method were widely used in clinical practice, and there was no difference in postoperative complications between the two methods in a previous small-case study. Therefore, it is unlikely that additional risk will arise from this study. In addition, all procedures are monitored by a trained anesthesiologist, and even if complications occur, appropriate treatment will be taken so that the possibility of additional risk to the patient is expected to be minimal.

11.7 Criteria for Discontinuation and Drop-out

- Withdrawal of consent

- Intubation with other alternative airway devices rather than standard laryngoscopy

- In a case of that cannot extubate after the surgery

- In a case of that should insert the nasogastric tube unexpectedly

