10.2 Exclusion criteria

- Symptoms of sore throat, hoarseness, and respiratory infections as assessed by a study

investigator at baseline

- Gastroesophageal reflux diseases defined by history taking from patients

- Congenital or acquired abnormalities of the upper airway

- Previous airway surgeries

- Previous history of aspiration

- Coagulation disorders

- History of difficult intubation or conditions with an expected difficult airway including Mallampati classification ≥3 or a thyromental distance <6.5 cm

- Use of airway instruments other than a direct laryngoscope such as a fiberoptic bronchoscope,

video laryngoscope, or lighted stylet

- Anticipated nasotracheal intubation or insertion of a nasogastric tube

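### Section 11.7 drops patients who are switched to another airway device after the allocated tube has failed, which conflicts with the planned intention-to-treat analysis and can favour noninferiority

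*Protocol*

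**What the plan says.** - **Allocation (Protocol, Section 11.2).** On enrolment, "an anesthesia nurse opens an envelope and prepares a tracheal tube with the allocated treatment". Allocation is therefore fixed before induction.
- **Device switch (Section 11.1).** A failed attempt is followed by a further attempt with a stylet. "When intubation fails in 3 attempts even using the stylet, other devices such, as a video laryngoscope" and similar instruments are then used. The switch is part of the study procedure, after the allocated tube has been tried.
- **Drop-out (Section 11.7).** Besides withdrawal of consent, the list contains "Intubation with other alternative airway devices rather than standard laryngoscopy", "In a case of that cannot extubate after the surgery" and "In a case of that should insert the nasogastric tube unexpectedly". It does not say whether a listed patient leaves the study or only one analysis set.
- **Outcome (Sections 11.1 and 11.5).** The primary outcome is "Incidence of sore throat during postoperative 24 h". Patients are asked at 0, 2, 4 and 24 h after surgery.
- **Analysis (Section 12).** "Both intention-to-treat and per-protocol analyses will be performed", with missing values filled by last observation carried forward (LOCF). Noninferiority is accepted if the upper 95% confidence bound is below 15%.
- **Sample size (Section 10.3).** 135 patients per group, raised to 300 in total for 10% dropout.

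**The concern.** A patient who follows the Section 11.1 pathway exactly can be dropped under Section 11.7 because of how intubation with the allocated tube went. The protocol itself records resistance to tube advancement as an outcome, so it treats ease of passage as something that lubrication might change. Repeated failed attempts are also a plausible cause of sore throat. If more dry tubes than wet tubes fail, the rule takes high-risk patients mainly out of the dry arm, and the observed difference shrinks towards a finding of noninferiority.

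Intention-to-treat needs an outcome for these patients in their allocated arm. If they are dropped at intubation, none has been collected. The intention-to-treat and per-protocol sets then lose the same patients, and neither analysis can serve as a check on the other. LOCF does not help: the first scheduled sore-throat assessment comes after surgery, so there is no postoperative score to carry forward. Answers not collected within 24 h cannot be recovered later.

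**Working it through.** **1. The plan's own figure.** With 57% in both groups, a 15-point margin, 80% power and one-sided 5%:

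n = (1.645 + 0.842)² × 2 × 0.57 × 0.43 / 0.15² = 6.183 × 0.4902 / 0.0225 = 134.7, so 135 per group.

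135 / 0.90 = 150 per group, 300 in total. Both stated figures reproduce. The allowance is 150 − 135 = 15 patients per group, so drop-outs are budgeted as patients who do not contribute to the required 135.

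**2. Order of events.** Envelope opened and tube prepared (11.2); three failed attempts (11.1); other device (11.1); drop-out criterion met (11.7); surgery; first sore-throat assessment at 0 h (11.1). The criterion is met after exposure to the allocated tube and before any outcome is observed.

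**3. Effect on the comparison.** The documents give no failure rate, so the drop-out fractions are assumptions. Others are:
- True incidences are 72% dry (57% plus the 15-point margin) and 57% saline, so any acceptance of noninferiority is an error.
- Every dropped patient has sore throat, which is the extreme case.
- 150 are randomised per arm and dropped patients are left out of the analysis.

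With fractions d (dry) and s (saline) dropped:

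Observed difference = (0.72 − d)/(1 − d) − (0.57 − s)/(1 − s)

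Type I error = Φ[(0.15 − difference)/SE − 1.96], where SE is the unpooled standard error with 150(1 − d) and 150(1 − s) patients. The 1.96 is the 95% interval rule of Section 12, which is one-sided 2.5%.

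| Dropped, dry vs saline | Dry − saline | Difference | SE | Type I error |
|---|---|---|---|---|
| None | 0.720 − 0.570 | 15.0 points | 0.0546 | 2.5% |
| 1% vs 0% | 0.71/0.99 − 0.57 | 14.7 points | 0.0548 | 2.8% |
| 4% vs 1% | 0.68/0.96 − 0.56/0.99 | 14.3 points | 0.0556 | 3.4% |
| 10% vs 0% | 0.62/0.90 − 0.57 | 11.9 points | 0.0568 | 7.9% |

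The last row puts the whole dropout allowance in the dry arm and none in the other.

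**4. Direction.** The bias towards noninferiority needs more drops in the dry arm. With 4% dropped in each arm under the same assumptions, the difference is 0.68/0.96 − 0.53/0.96 = 0.15/0.96 = 15.6 points, slightly against noninferiority. If the arms have the same incidence and lose the same number, the difference stays at zero.

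**The case against.** The strongest reply is that Section 11.7 is a bare list. It does not say that assessments stop or that patients leave the intention-to-treat set. Because Section 12 plans both analyses, the list could be read as defining the per-protocol set, and that mapping is often left to a statistical analysis plan. This stands in part: the loss of outcomes is inferred from the word drop-out, the 10% allowance and the 0 h first assessment. But the heading speaks of discontinuation, and a site that follows it literally would stop collecting data. A later analysis plan cannot restore answers that were never taken.

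The second reply is that switches will be rare. Section 10.2 excludes expected difficult airways, the operator has ten years' experience, and three attempts come first. This also stands, and it makes the 10% vs 0% row an outer bound.

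Four stronger readings are tempting, and the documents do not support them:
- **All three airway rules remove the hardest intubations.** The unplanned nasogastric tube and failed extubation also come after randomisation, but nothing ties them to tube lubrication or to difficult intubation.
- **Dropped patients would be counted as free of sore throat through LOCF.** This needs the symptom-free eligibility screen in Section 10.2 to be treated as a score to carry forward. Scores are scheduled only after surgery, and the protocol does not name the screen as a baseline value.
- **The intention-to-treat analysis certainly has no outcome for these patients.** That is the likely result of the wording, but it is not stated.
- **Section 10.2 excludes patients after randomisation.** The item "Use of airway instruments other than a direct laryngoscope such as a fiberoptic bronchoscope" stands in an eligibility list directly before one about anticipated nasal intubation. Planned use is the natural reading.

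**Conclusion.** The point holds for the device-switch rule. As written, it drops randomised patients on an event that the allocated tube may influence, before their outcome is seen, and this is at odds with the intention-to-treat analysis in Section 12.

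The effect is probably small. At the margin, and with sore throat in every dropped patient, type I error rises from 2.5% to about 2.8% for 1% vs 0% dropped and to 3.4% for 4% vs 1%. It reaches about 8% only in the extreme 10% vs 0% case. These figures rest on assumed failure rates and on more failures in the dry arm; the protocol supports neither with data. The change should be made because it is cheap and the data cannot be recovered later, but nothing here shows that the trial's conclusion would be invalid without it.

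**What to change.** State in Section 11.7 that the criteria other than withdrawal of consent remove a patient from the per-protocol set only. These patients still receive the scheduled sore-throat assessments wherever they are able to respond, and they are analysed in their allocated arm in the intention-to-treat analysis. The schedule, the outcome window and clinical care stay as they are. A patient who is still intubated may be unable to answer at the early time points, and the wording allows for that.

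The cost is a few sentences of protocol text and a few more patients seen by the same blinded assessor. The change should be in place before enrolment starts, or as soon as possible if it has begun.
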